### Sample size

We aim to enroll 90 participants. Assuming an attrition rate of 20%, we will have a final sample of 72 women with data through a 20-week follow-up. This sample size is appropriate for early-phase developmental trials [60]. While we do not intend to fully power our exploratory aim 3, we do anticipate sufficient power to detect a large effect (to detect a large effect of Cohen’s *d* = .80) between a treatment arm and control group on primary (PTSD symptoms) and secondary (anxiety, depression, self-compassion, emotional regulation, sleep disturbance) outcomes with *n* = 72 (*p* < 0.05, power = 0.80). The power of the study is such that large effects will be detectable and the directionality of effects will be sufficiently stable to assess the preliminary merit of the intervention and provide information needed for future larger studies. Effect sizes will be calculated along with tests of significance. Effects of intervention on physical activity, mindfulness, and perceived exertion will be explored using mixed models or multilevel models to examine multiple waves of data from weekly logs and GENEActiv. Effects of intervention should emerge as significant regression coefficients for the group membership predictor in accounting for within-person intercepts and slopes. Planned contrasts will compare three groups (LD, MD, and control) for differing trajectories over time. If both yoga groups show greater improvements on outcomes than the control group and there are significant differences between LD and MD, this would indicate that one group may lead to improved outcomes. If both yoga groups improved more than the control group, and there are *no* significant differences between LD and MD, we will use feasibility data to determine which group is more feasible.

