### Data management

The research participant will self-report data electronically via Qualtrics. Weekly, the research team will be responsible for ensuring the completeness and timeliness of the data reported by the participants. Additionally, the research team will skim the data after each collection time point to ensure it is complete and will follow-up with any participants in which data collection is not complete.

Data quality will be monitored throughout the study. Measurement values will be compared to their known ranges. Out of range values will be investigated and either corrected if possible or treated as missing data. Statistical analyses will adjust for baseline demographic characteristics when statistically appropriate. Multiple imputations will be used to conduct statistical analysis with missing data. In the event that the missing at random assumption is violated, we will model the missing data mechanism and conduct sensitivity analysis on model parameters.

We have multiple strategies in place to identify yoga participation both during video sessions and outside of video sessions. First, we will be collecting 24-h, time-stamped GENEActiv accelerometer data at baseline, post-intervention (12 weeks), and follow-up (20 weeks) and will have a full record of their activity level during these time points. We will also be monitoring UDAYA website log-in information and will be able to localize activity monitor data while the participant is logged into the website and using the yoga videos. This will allow us to verify whether the participant is being active during the times they are using the website. Second, we will collect self-reported minutes of yoga using a log. This self-report log will also give us a time stamp of yoga activity that we will be able to cross-refer to the accelerometer data. Finally, we will be able to monitor all other physical activities that are performed outside of yoga, examining whether the intervention may have unintended effects of activity within other types of physical activity. Collectively, we will have a full record of yoga and physical activity (outside of yoga) participation that we will be able to use to understand the “dosage” that is being achieved for this trial.

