### Statistical analysis

Inferential analyses: To examine quantitative feasibility measures, we will use Fisher’s exact tests when expected cell counts <5 and *t* tests to compare feasibility scores between the low and moderate dose groups. Significant differences between the two groups will indicate which yoga group is more feasible. We will also use logistic and Gaussian regression analyses to further compare feasibility scores between groups while adjusting for baseline participant characteristics.

We will use Fisher’s exact tests and ANOVAs to compare quantitative acceptability scores across control and yoga groups. Logistic and Gaussian regression analyses will be used to compare scores while adjusting for baseline participant characteristics. We expect participants in the control group to report similar levels of acceptability compared to those in the yoga groups, but participants in the yoga groups are expected to report greater improvements on outcomes than control participants.

Descriptive analyses: SPSS and *R* will be used to conduct descriptive statistical analyses, including graphical analysis (e.g., scatter plots, boxplots and histograms) and data summarization (e.g., means, medians, ranges, cross-tabulations) to identify data entry errors, outliers, and non-normal distributions. Standard errors and confidence intervals will be calculated using either parametric or non-parametric methodology, including the use of the bootstrap to estimate standard errors when parametric assumptions fail.

Data from the qualitative interviews will be transcribed and independently coded by the research team using NVivo. After coding is complete, researchers will meet to reach agreement on major themes of the interviews. Once the major themes have been determined, findings will be verified through member checking to determine accuracy of findings. Principal Investigator (PI) [name] and Co-I [name] have extensive training and experience in qualitative methods.

Psychometric analyses: We will evaluate scale reliabilities using Cronbach’s alpha coefficients based on baseline (T1) data. Scale inter-correlations will be estimated along with complete descriptive statistics on scale items.

Randomization check: We will also conduct an ANOVA to compare the experimental and control groups on outcome and demographic variables at baseline.

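### The stated power of 0.80 for d = 0.80 is slightly generous at 24 women per arm, and the adjustment named in the plan omits the baseline outcome that could make up the difference

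*Protocol article*

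**What the plan says.** The Sample size section of the protocol article starts from "We aim to enroll 90 participants" and continues: "Assuming an attrition rate of 20%, we will have a final sample of 72 women with data through a 20-week follow-up". For the efficacy aim, which it describes as exploratory and not meant to be fully powered, it states "we do anticipate sufficient power to detect a large effect", specified as Cohen's d = 0.80 at p < 0.05 and power 0.80. The contrast is "between a treatment arm and control group on primary (PTSD symptoms"), and the same figure is extended to anxiety, depression, self-compassion, emotional regulation and sleep disturbance. Neither the test nor its sidedness is given. The section adds that "the directionality of effects will be sufficiently stable to assess the preliminary merit of the intervention".

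On adjustment, the Data management section says: "Statistical analyses will adjust for baseline demographic characteristics when statistically appropriate". The Statistical analysis section plans regressions adjusted for participants' baseline characteristics, but for feasibility and acceptability scores. Under the label of a randomization check it adds: "We will also conduct an ANOVA to compare the experimental and control groups on outcome and demographic variables at baseline".

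Table 3 (Summary of data collection) shows the IES-R, the anxiety, depression, self-compassion and emotional regulation scales and the sleep measures all taken at baseline, 12 and 20 weeks. The mixed or multilevel models in the Sample size section are named for physical activity, mindfulness and perceived exertion.

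**The concern.** Two things stand out. First, 72 women in three equal arms is 24 per arm, and the familiar requirement for d = 0.80 with 80% power is a little more than that, so the stated power looks optimistic.

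Second, the plan names a weak form of adjustment. Demographics may or may not predict a PTSD symptom score; the same score at baseline usually will. The condition attached to the demographic adjustment is not defined, so the covariate set could be chosen after the data are seen. A significance test of baseline differences between properly randomized arms can only pick up chance, so it gives no basis for that choice.

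What is at stake is precision. With 24 women per arm the estimates will be wide, and the article intends them to inform a larger trial. Baseline scores that are already being collected could narrow them.

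**Working it through.** **Inputs.** From the Sample size section: 90 enrolled, 20% attrition, d = 0.80, alpha 0.05, power 0.80, one yoga arm against control. From Study design and Allocation: three equal arms (30 each, blocks of six). Assumed: a two-sided test, since sidedness is not stated.

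**1. Evaluable number.** 90 × 0.80 = 72, and 72 / 3 = 24 per arm. The attrition arithmetic is correct.

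**2. The plan's own figure.** The standard error of a standardized difference is √(2/24) = 0.289, so the noncentrality is 0.80 / 0.289 = 2.771. The normal approximation gives Φ(2.771 − 1.960) = Φ(0.811) = 0.791, which is within one point of the stated 0.80. This may be how the figure arose.

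**3. Other standard calculations at 24 against 24.**

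| Method | Power at d = 0.80 | d detectable with 80% power |
|---|---|---|
| Normal approximation, two-sided | 0.791 | 0.81 |
| t, error pooled over three arms (69 df) | 0.780 | 0.82 |
| Two-sample t test (46 df) | 0.774 | 0.83 |

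No two-sided unadjusted method reaches 0.80. The two-sample t test gives 0.791 at 25 per arm and 0.807 at 26, so the shortfall is one or two women per arm depending on the method (the normal approximation needs 25). A one-sided test would give 0.86 (t) to 0.87 (normal).

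**4. Adjusting for the baseline value of the outcome.** If r is the correlation between baseline and follow-up, the residual standard deviation shrinks by √(1 − r²). The noncentrality becomes 0.80 / (0.289 × √(1 − r²)), with 45 df for two arms and one covariate. The article gives no r, so a range is shown.

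| Assumed r | 0.80 / √(1 − r²) | Power |
|---|---|---|
| 0 | 0.80 | 0.774 |
| 0.2 | 0.82 | 0.790 |
| 0.3 | 0.84 | 0.811 |
| 0.5 | 0.92 | 0.879 |
| 0.7 | 1.12 | 0.967 |

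Power passes 0.80 at r of about 0.26. Even at r = 0 essentially nothing is lost.

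**5. Direction of effect.** The chance that one contrast has the wrong sign is Φ(−d / 0.289): about 0.3% at d = 0.80, 4% at 0.5, 15% at 0.3 and 24% at 0.2. The direction is stable for large effects, and not for small ones.

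**The case against.** The strongest reply is that the power shortfall is close to rounding. The normal approximation gives 0.79, the aim is declared exploratory, and a gap of one to three points is small beside the uncertainty in a guessed 20% attrition rate. That stands, and it is why the power figure alone is a minor correction.

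A second reply is that covariates are normally fixed in an analysis plan, which is not shown, and that the Sample size section plans contrasts of trajectories, which would draw on baseline scores. This stands in part. An article need not list covariates, but this one does state an adjustment rule, and that rule is conditional and confined to demographics. The mixed models are not clearly assigned to PTSD symptoms. A trajectory contrast is also not automatically equivalent to adjustment: if it amounts to comparing mean changes from baseline, power at d = 0.80 is 0.63 at r = 0.3 and 0.77 at r = 0.5.

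Third, the gain depends on r. Entry requires an IES-R score of at least 33, and restricting the range in this way may lower the correlation. At r = 0.2 power is still 0.79.

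Some stronger readings are tempting but not supported:

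- **The power should be given as 0.66.** Simulation with a shared control gives about 0.66 for both yoga arms being significantly better than control when both have d = 0.80. The article claims power for one contrast only, and does not say that greater improvement in both arms must be significant.
- **The baseline ANOVA determines the adjustment.** It is labelled a randomization check, and nothing links its result to the choice of covariates.
- **The wrong-sign risks of 15% and 24% refute the claim about direction.** They apply to small effects, for which no power is claimed. The sentence opens with large effects; its fault is only that the second half carries no such limit.
- **Time since stillbirth is a known source of variation that must be adjusted for.** The document gives no evidence of this.

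**Conclusion.** The point holds in a modest form. With 24 women per arm, an unadjusted two-sided 5% comparison has power 0.77 to 0.79 for d = 0.80, not 0.80, and the effect detectable with 80% power is 0.81 to 0.83. This is a small overstatement for an aim the article does not intend to power fully, and it changes no decision in the trial.

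The adjustment rule matters more. It is conditional, names only demographics, and leaves out the baseline value of the outcome, although that is collected for every powered outcome. Prespecifying it would lift power above 0.80 if the baseline correlation is at least about 0.26. That correlation is an assumption; the size of the gain cannot be fixed from the document.

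The result rests on a two-sided test, equal arms after attrition, and a common standard deviation.

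**What to change.** - Replace the conditional demographic adjustment in Data management with a fixed rule: PTSD symptoms and each secondary outcome are adjusted for their own baseline value, whatever imbalance is observed. The self-report baselines are completed before randomization. The accelerometer baseline week falls after it (Study enrollment, Phase 2), so for sleep the plan should state which baseline measure is used.
- Report baseline characteristics by arm descriptively, in place of the ANOVA tests.
- Restate the unadjusted power as about 0.77 to 0.79 per contrast, naming the test and its sidedness. If adjusted power is quoted, give it as a range with the assumed correlations: 0.79, 0.81, 0.88 and 0.97 at 0.2, 0.3, 0.5 and 0.7.
- Limit the statement about the stability of direction to large effects.

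The cost is revised wording in three sections. No additional participants, visits or measurements are needed.

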### Recruitment

We will nationally recruit and screen participants via a web-based survey (i.e., Qualtrics). We will work with non-profit partners who provide support for bereaved parents (e.g., MISS Foundation, Star Legacy Foundation) to actively recruit participants. We will also heavily utilize web-based strategies including social media (i.e., Facebook, Twitter), social networking sites, online stillbirth support groups (e.g., SOBBS, Compassionate Friends), and email LISTSERV. We will make a concerted effort to recruit minority women utilizing the information learned from the interviews with minority women in phase 1. Note: recruitment for the iterative design process in phase 1 will involve contacting *local* organizations following the same strategies above.

### Study enrollment

Interested participants will complete an eligibility screener (approximately 5–10 min) on Qualtrics. The screener will only allow one entry per IP address to prevent “ballot box stuffing.” Additionally, there will be a final question on the screener asking the participant to confirm all responses. Upon submitting the screener, participants will no longer have access to the screener. Research team members will follow an Institutional Review Board (IRB)-approved script to respond to interested participants who phone or email and refer them to the eligibility screener (participants provide consent electronically to complete the eligibility screener). All ineligible participants will be notified by phone and/or email and offered a discounted Udaya.com membership ($9/mo., compared to $12/mo.)

#### Phase 1

Iterative design: Eligible participants (see Table 1 for eligibility criteria) will receive an email requesting times to schedule their first visit to the lab on the university campus. During the participant’s first visit, they will complete an informed consent document.

Interviews: Eligible participants will receive an email requesting times to schedule their 15–20-min phone interview. Following, participants will be sent a Qualtrics link asking them to electronically sign an informed consent document before their scheduled interview.

#### Phase 2

Eligible participants (see Table 2 for eligibility criteria) will be asked to complete a phone intake appointment, an electronic informed consent, a HIPAA authorization form, and baseline assessments of self-report measures (see Table 3). Participants will then be randomized to an intervention (LD or MD) or control group. The research team will mail intervention group participants: (1) a packet with study info and directions, (2) a document including strategies to overcome barriers to online yoga participation, (3) an accelerometer (GENEActiv) with instructions on how to wear, and (4) a yoga mat, two blocks, and a strap. The control group will receive (1) a packet with study info and directions, (2) a document including strategies to overcome barriers to online physical activity participation, (2) an accelerometer (GENEActiv) with instructions on how to wear and a pre-paid return mailer, and (3) a stretching mat and band. All participants will be asked to begin wearing the GENEActiv immediately upon receiving it for one full week and then mail monitor back in a pre-paid envelope supplied in their packet. The GENEActiv will be mailed to participants again at post-intervention (12 weeks from baseline) and follow-up (20 weeks from baseline) using the same process. When participants have worn the GENEActiv for 1 week, they will be emailed their UDAYA username and password to begin accessing their respective videos.

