**Fig. 1 Fig1:**
[figure not shown]
Study flow chart: the *left side* of the diagram illustrates the flow of the study for phase 1, and the *right side* illustrates the phase 2

#### Phase 1

Part A. Iterative design: We will develop the yoga prescription using an iterative design process with the following steps:Identify 30 videos from the existing UDAYA (an online-streaming commercial yoga website; https://udaya.com) library.Gather a panel of women whose babies were stillborn (*n* = 5) and a panel of women who are regular yoga practitioners and have not experienced a baby’s death (*n* = 5) to review (i.e., watch or engage) yoga videos selected from step one above.Develop (produced by Udaya.com) up to 12, 30-min yoga videos specifically for the grieving mothers.

Part B. Interviews to identify cultural barriers to recruitment: We will recruit five non-Caucasian (predominately Hispanic and/or African American) women who have experienced stillbirth to participate in a 15–20 min phone interview. These interviews will guide the recruitment process for phase 2, and additional recruitment materials will be developed to ensure adequate enrollment of non-Caucasian women in the study. The interview questions will consist of questions related to:Perceptions/opinions about yoga related to physical and mental health.Strategies to ensure adequate enrollment and retention of non-Caucasian women to participate in a yoga intervention.

#### Phase 2

Phase 2 is a three-group randomized feasibility trial with assessments at baseline and at 12 and 20 weeks from baseline. After completion of the consent process and the baseline assessment, 90 women will be randomized into one of the following three arms for 12 weeks: (1) intervention low dose (LD) = 60 min/week yoga (*n* = 30), (2) intervention moderate dose (MD) = 150 min/week yoga (*n* = 30), or (3) stretch and tone control (STC) group = 60 min/week of stretching/toning exercises (*n* = 30).

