### Allocation (phase 2 only)

Block randomization will be used to assign participants to treatment groups. Specifically, the biostatistician will construct 15 blocks of six participants using SAS PROC PLAN with a random number seed known only by the biostatistician. This will be done at the beginning of the study (front-loaded) and provided to a research staff member not associated with this study (i.e., trusted broker). The trusted broker will utilize the treatment allocations to sequentially assign enrollees to randomized treatment groups (the biostatistician will be shielded from enrollment date and enrollment order, and participant IDs will not reflect enrollment order). The trusted broker will hold the codes that match participants to treatment groups. Research staff members will call the trusted broker to determine assignment to group. In case of adverse events (AE), the research staff member will call the trusted broker to provide for unblinding (AE only). After randomization, participants will be emailed a study information packet (i.e., instructions, UDAYA username/password) according to the intervention assigned. The initiation of the study will begin after allocation to study arm (see Fig. 2 for phase 2 study flow chart).

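### The GENEActiv baseline week is worn after randomisation with the arm-specific kit in hand, so it is not a pre-randomisation baseline for objective sleep and physical activity

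*Protocol article*

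**What the plan says.** The Protocol article describes the order of steps in several places.

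- **Study design, Phase 2:** "After completion of the consent process and the baseline assessment, 90 women will be randomized". Table 3 lists GENEActiv at baseline, 12 and 20 weeks, for both sleep quality and physical activity.
- **Study enrollment, Phase 2:** consent and the self-report baseline come first, and the text goes on: "Participants will then be randomized to an intervention (LD or MD) or control group. The research team will mail intervention group participants". The yoga parcel then includes "3) an accelerometer (GENEActiv) with instructions on how to wear, and (4) a yoga mat, two blocks, and a strap"; the control parcel includes "an accelerometer (GENEActiv) with instructions on how to wear and a pre-paid return mailer, and (3) a stretching mat and band". Each parcel also holds an advice sheet on barriers, worded for online yoga or for online physical activity. "All participants will be asked to begin wearing the GENEActiv immediately upon receiving it for one full week". The video login is emailed once that week has been worn.
- **Allocation (phase 2 only):** "After randomization, participants will be emailed a study information packet (i.e., instructions, UDAYA username/password) according to the intervention assigned". No wait for the wear week is mentioned.
- **Procedures:** accounts are assigned on enrolment and credentials are supplied before participation begins, again with no mention of the wear week.
- **Use of the data:** Sample size plans mixed or multilevel models on GENEActiv waves, with contrasts of trajectories across the three groups. The randomisation check under Statistical analysis compares groups on outcome variables at baseline. Data management says accelerometry will help "verify whether the participant is being active during the times they are using the website".

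**The concern.** A baseline has to be measured before the participant knows her arm if it is to be independent of allocation. Here the woman opens a parcel that shows whether she is in a yoga or a stretching group, and wears the device for the following week. She may become more active or change her sleep routine in anticipation, or may be disappointed and do less. If such reactions differ between arms, the first GENEActiv wave already carries a group difference, and any contrast that starts from that wave inherits it.

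Two further consequences follow. Women lost between allocation and wear have no accelerometer baseline, and that loss may differ by arm. The randomisation check, applied to GENEActiv variables, could not separate chance imbalance from a response to allocation.

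The safeguard in Study enrollment, that the login is held until the wear week is over, makes the week pre-video. Allocation and Procedures do not repeat the hold, so staff working from those sections could release the videos during the week that is meant to be baseline.

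**Working it through.** **Order of steps**

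1. Study enrollment gives this sequence: consent and self-report baseline; randomisation; parcel with device and arm-specific kit; 7-day wear; login.
2. Study design read with Table 3 gives a different one: baseline assessment, including GENEActiv; then randomisation.
3. For the accelerometer these cannot both be followed. For self-report measures they agree.
4. On login, Study enrollment places it after the wear week. Allocation says only that it comes after randomisation, and Procedures only that it comes before participation. The last two can be read as compatible with the first, but neither states the hold.

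**What a post-allocation shift would do**

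The protocol gives no figure for such a shift, so the following is illustration. Inputs from Sample size: 90 enrolled and 20% attrition, so 90 × 0.8 = 72, or 24 per arm. As a check on that base, power for d = 0.80 at two-sided 0.05 is Φ(0.80/√(2/24) − 1.96) = Φ(2.771 − 1.960) = 0.79, against the stated 0.80 (0.774 by t test). Nothing below depends on the power figure.

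Assumptions: the baseline week differs between a yoga arm and control by s SD because of allocation; the shift does not persist to follow-up; there is no true effect; baseline and follow-up correlate at r = 0.3 to 0.7.

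- Change score: bias = −s; standard error = √(2(1 − r)) × √(2/24).
- Baseline-adjusted: bias = −r·s; standard error = √(1 − r²) × √(2/24).
- Example, s = 0.2 and r = 0.5: the change-score standard error is 1 × 0.289, the standardised bias is 0.2/0.289 = 0.69, and the two-sided rejection rate is 0.107. Adjusted: bias 0.10, standard error 0.866 × 0.289 = 0.25, rejection rate 0.069.

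| Assumed s (SD) | Change-score bias | Type I error, r 0.3–0.7 | Adjusted bias | Type I error, r 0.3–0.7 |
|---|---|---|---|---|
| 0.1 | −0.10 | 0.060–0.073 | −0.03 to −0.07 | 0.051–0.063 |
| 0.2 | −0.20 | 0.090–0.145 | −0.06 to −0.14 | 0.055–0.104 |
| 0.3 | −0.30 | 0.142–0.269 | −0.09 to −0.21 | 0.062–0.175 |

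The sign is shown for a positive s; a negative s reverses it.

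**Link to the planned model**

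For a straight-line slope through waves at 0, 12 and 20 weeks, the mean time is 32/3 = 10.67 and the sum of squared deviations is 113.78 + 1.78 + 87.11 = 202.67. The first wave has weight −10.67/202.67 = −0.0526 per week. Over 20 weeks the slope contrast therefore moves by 20 × 0.0526 × s = 1.05s, about the same as a change score. This assumes complete data and that time is modelled linearly, which the article does not specify.

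**Overlap with video use**

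If the login is held, the baseline week precedes all video use and the 20-week wear follows the 12 prescribed weeks. Only the wear around week 12 can overlap, so at most 1 of 12 intervention weeks is covered.

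**The case against.** The strongest reply has four parts, and most of it stands.

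First, the stated hold on the login means the week is meant to be free of study videos. That removes the most obvious route for an arm effect and leaves reactivity to knowing the arm.

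Second, the kits are parallel in kind, so reactivity common to all arms cancels. LD and MD receive the same listed equipment, so the kit mainly separates yoga from control.

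Third, the article names no change-score analysis and no adjustment for a GENEActiv baseline. The adjustments it mentions are for demographic or participant characteristics. The exposure is through the group trajectories in the mixed models, where physical activity is named explicitly.

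Fourth, this is a feasibility trial with exploratory efficacy aims, and its benchmarks do not use accelerometer data.

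It can also be argued that the baseline assessment in Study design means the self-report battery alone, since Procedures mentions wearing the device and completing assessments as separate tasks. That reading is possible, but Table 3 places GENEActiv in the baseline column with everything else. Even if the contradiction is explained away, the week is still post-randomisation.

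A reader might go further and infer that the sleep outcome has no clean baseline, or that women who leave before wear have no baseline at all. Neither follows. The PSQI, whose higher scores the article describes as more sleep disturbance, is self-report and precedes randomisation, as do the IES-R and the other questionnaires. Women lost before wear lack only the accelerometer week.

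Nor does the limited overlap with video use mean that dose goes unmeasured. Data management ties accelerometry to the three time points, and web tracking and logs run throughout the intervention.

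**Conclusion.** The point holds in a limited form. Under Study enrollment, every GENEActiv baseline is recorded after randomisation, with the arm visible at least as yoga versus control. This conflicts with Study design read with Table 3. The week is intended to be pre-video, but two other sections do not state the hold that makes it so.

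Bias in the GENEActiv contrasts over time is possible, not demonstrated. A reader might infer that it necessarily dilutes the yoga effect. The documents do not support that: the shift could go either way, and its size cannot be derived. The 0.1 to 0.3 SD shifts and the correlations of 0.3 to 0.7 are assumptions chosen to show scale.

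Severity is moderate and confined to exploratory accelerometer outcomes. The feasibility benchmarks, the IES-R and all other self-report baselines are untouched. It still deserves correction before enrolment, because the order cannot be repaired after the data are collected.

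**What to change.** 1. After consent and the self-report baseline, mail the accelerometer alone.
2. Call the trusted broker only after the 7-day wear is complete, then send the arm-specific kit and the login.
3. Make Study design, Procedures, Study enrollment and Allocation state this one order, including when credentials are released.
4. In Data management, say that accelerometer verification of video use applies only to wear weeks that overlap prescribed video use.

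The cost is one extra outbound parcel per woman (90 in all if every woman is enrolled) and an estimated 1 to 2 weeks between consent and randomisation. The self-report baseline would be older by the same interval at allocation. Some women may drop out in that interval, but before randomisation rather than after it.

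If the present order is kept, label the week post-randomisation, do not use it as a baseline covariate or as the origin of change, compare arms on the 12- and 20-week GENEActiv values, and leave GENEActiv variables out of the randomisation check. This costs no parcels but gives up the precision that a true accelerometer baseline would bring. The login hold should then be stated in all three sections that mention credentials.
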